## Abstract

**Background:**

Dialysis-related myofascial pain in hemodialysis (HD) patients is an important issue that is associated with many other psychosomatic problems. Effective interventions are required to alleviate pain in this group. Chinese herbal medicine (CHM) may be a potential therapeutic treatment for reducing pain. The aim of this study is to evaluate the effects of a classic CHM formula intervention on pain intensity, daily function, quality of life (QOL), and safety in patients receiving HD in a dialysis center within the context of southern Taiwan.

**Methods:**

This will be a randomized, open label, cross-over trial with two parallel groups in a pre- and post-test study. Forty patients reporting myofascial pain related to the arteriovenous (AV) fistula in the arm during regular HD sessions will be recruited. Participants will receive 4 weeks of treatment with Juan Bi Tang (JBT) and 4 weeks of no treatment in a random order, separated by a washout period of 2 weeks. Treatment doses (3 g JBT) will be consumed thrice daily. The primary outcome measure will be the Kidney Disease Quality of Life 36-Item Short-Form Survey. Secondary outcomes will include the Fugl-Meyer Assessment-arm, Visual Analogue Scale (VAS) of pain, and grip strength. Outcomes will be collected before and after each intervention, for a total of four times per participant. The safety evaluation will focus on adverse events (AEs).

**Discussion:**

This study will be the first to use CHM to treat patients receiving HD with dialysis-related myofascial pain in their fistula arm and to perform a complete assessment of the treatment, including records of QOL, arm function and muscle power, severity of pain, and safety. The results of the study will provide convincing evidence on the use of JBT as an adjuvant treatment for dialysis-related myofascial pain.

**Trial registration:**

Clinicaltrials.gov registry (NCT04417101) registered 30 May 2020.

## Background

Myofascial pain syndrome (MPS) is characterized by localized pain (1), paresthesia, exquisite tenderness, restricted range of motion, and hypersensitivity at specific anatomic sites, which are termed taut bands with active myofascial trigger points (MTrPs) (2–4). According to the International Association for the Study of Pain and the American Academy of Pain Medicine, the essential criteria for the diagnosis of MPS are hypersensitive spots that cause local pain and symptoms that can be recreated by palpation (5). In the United States, about 9 million people have MPS (6), and its prevalence in the general population is between 9 and 85% (5, 7).

Myofascial pain syndrome is often more serious in females than in males, and its prevalence apparently increases with age (8). Currently, the etiology of MPS is poorly understood, but various aspects of its pathogenesis are being investigated (8, 9). The negative effects of MPS on quality of life (QOL), such as loss of work tolerance, fatigue, and weakness, are well-documented (10). However, few studies have focused on MPS in specific populations.

One major complication of chronic kidney disease (CKD) or end stage kidney disease (ESRD) is rheumatic disorders, and over half (60%) of patients receiving hemodialysis (HD) develop musculoskeletal disorders (11). Therefore, it is important to consider a differential diagnosis of MPS in these patients. Another form of MPS which sometimes develops in patients receiving HD is related to the fistula arm. In such cases, the symptoms are induced by factors implicated in or related to maintenance HD.

Factors such as comorbidities, dialysis type, metabolic disorders, nutritional factors, biomechanical imbalance, and/or physio-psychological deconditioning may simultaneously contribute to the development of dialysis-related myofascial pain (12, 13). However, the pathological mechanisms involved are not well-known. Currently, the underlying pathologies are considered to be local injury from gross venipuncture or constant micro-trauma from venous pressure during each HD session in the affected arm muscle (8, 14). This stress can lead to inappropriate acetylcholine (Ach) activity at the endplate. Such activity can cause an energy crisis that favors the release of nociceptive neurotransmitters. The altered ACh in turn triggers an active contractile phenomenon (taut bands), and the nociceptive neurotransmitters, which compensate for tissue hypoxemia, cause pain neurotransmission or sensations in the form of local pain and referred pain (15–17).

There is no definitive treatment for dialysis-related myofascial pain, and the most common treatment modality is based on condition-specific and stepwise pain management for ESRD (18, 19). Aspects of dialysis-related myofascial pain can be easily mitigated with non-steroidal anti-inflammatory drugs (NSAIDs), Cyclooxygenase-2 (COX-2) inhibitors or topical analgesics (18). One problem with this approach to pain management is that the use of oral analgesics may have side effects such as bleeding, fluid retention, and cardiovascular events; thus, they are not appropriate for all patients (20). In addition, some sedative-hypnotic agents or muscle relaxants for alleviation of symptoms of anxiety and/or depression carry risks of hypotension and physical dependence (21, 22).

The aforementioned limitations of conventional treatment have led to the present study, which advocates the use of Chinese herbal medicine (CHM) therapy for pain management. CHM therapy is safe and inexpensive, and it can alleviate the pain and anxiety associated with several diseases (23, 24). Moreover, CHM use by patients with CKD has positive results on reducing the risk of ESRD, as determined by thorough analysis of the classification of CHM prescriptions in the Taiwan National Health Insurance Research Database (25). Juan Bi Tang (JBT) has a long history of use as a classic herbal prescription for treating Bi syndrome and was first documented in a classical Chinese medical book, *Prescriptions for Ji Sheng Fang* (CE 1253). As joint pain is one of the most common symptoms of Bi syndrome, some scholars often translate it as “Arthralgia syndrome.” Clinically, Bi syndrome covers many musculoskeletal diseases, such as rheumatoid arthritis, osteoarthritis, rheumatism, fibromyalgia, or myofascial syndrome (26). The basic pathology of Bi syndrome is the obstruction of *qi* (also called vital energy) and blood in the meridians due to the invasion of pathogenic wind, cold, and dampness. According to traditional Chinese medicine (TCM), open meridians and normal circulation of the *qi* and blood are associated with an absence of pain, while obstruction of the meridians and the flow of *qi* and blood are associated with the presence of pain. Juan Bi Tang is used for treating pain in the upper limbs by warming up meridians so as to dissipate cold, eliminate dampness, activate the *qi* and blood, and also resolve stasis (27). Although JBT is widely used in the treatment of musculoskeletal disorders, no studies have been conducted to examine its efficacy and safety for the treatment of dialysis-related myofascial pain in patients receiving HD. This randomized, open label, parallel-group, cross-over, single center clinical trial will aim to determine the possible benefits of JBT in patients with dialysis-related myofascial pain.

## Methods/Design

### Study design

This single-center, two-phase study will last 12 weeks. It will be a randomized, prospective, crossover, open-label study comprising two groups and two treatment sequences, each consisting of 4 weeks of daily treatments separated by a 2-week washout period (Figure 1). In total, 40 patients will be recruited (20 patients per group) from a dialysis center in Chang Gung Memorial Hospital (CGMH), Kaohsiung, Taiwan. The subjects will be randomly and equally assigned with a central registration method into group A (JBT course in period I but not in period II) or group B (JBT course not in period I but in period II). The research protocol has been approved by the Ethics Committee of the CGMH (202000477A3) and registered at ClinicalTrials.gov (NCT04417101). The Standard Protocol Items: Recommendation for Interventional Trials (SPIRIT) 2013 checklist is provided in Table 1.

**Figure 1 F1:**
[figure not shown]
Study design from enrollment to analysis following the CONSORT 2010 flow diagram.

**Table 1 T1:** Summary of collected data at each time point according to SPIRIT 2013 guidelines.

**Testing variables**	**Screening**	**Randomization**				**Follow-up**
	**Week 1**	**Week 0 (baseline)**	**Week 4**	**Week 6**	**Week 10**	**Week 12**
Inclusion and exclusion criteria	X					
Baseline information	X					
Inform consent	X					
Intervention						
Period I		X	X			
Period II				X	X	
Assessment						
VAS		X	X	X	X	X
KDQOL-36		X	X	X	X	X
FMA-UE		X	X	X	X	X
Griping force		X	X	X	X	X
Laboratory data		X	X	X	X	X
Conditional information			X	X	X	
Adverse events			X	X	X	X

VAS, visual analog scale; KDQOL-36, Kidney Disease Quality of Life 36-Item Short-Form Survey; FMA-UE, Fugl-Meyer Assessment for upper extremity.

### Study participants

Participants will be recruited from Kaohsiung CGMH via posters and advertisements on the official hospital website. The recruitment period is planned to last 18 months. All participants will provide informed consent before randomization. The schedule of patient enrollment, intervention, and assessment is illustrated in Table 1.

### Eligibility criteria

#### Inclusion criteria

Participants meeting the following criteria are eligible:

Age of 20 years or older;Treatment with conventional HD three times a week via an arteriovenous (AV) fistula for at least 3 months;Myofascial trigger points in one or more muscles around the AV fistula, namely, the brachioradialis, the flexor carpi radialis, the palmaris longus, and/or the pronator teres (Figure 2), accompanied by dialysis-related myofascial pain presenting during HD and diagnosed by a nephrologist (28);Onset of symptoms within 1 month before enrollment;Exquisite tenderness on palpation in the taut band, with moderate intensity of pain at baseline (i.e., a pain score >3 on a numeric rating scale);No change of painkillers, muscle relaxants, or anti-inflammatory medications and no use of topical anesthetics in the past week.

**Figure 2 F2:**
[figure not shown]
Muscles of the anterior forearm around the arteriovenous fistula (x: trigger points of the biceps brachii).

#### Exclusion criteria

The exclusion criteria are as follows:

Severe systemic disease (i.e., sepsis, cancer, coagulopathy) interfering with therapy attendance;Comorbid conditions such as rheumatoid arthritis, stroke, chronic liver disease, radiculopathies of the upper limb, recent history of cervical/shoulder/arm surgery, or trauma;Depression and/or presence of a psychiatric disorder;Treatment with CHM for dialysis-related myofascial pain in the past month;Allergic reactions (i.e., skin rash, purpura, and vasculitis) to CHM;Inability to comprehend or sign an informed consent form.

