#### Subject withdrawal criteria

Study participation will be terminated under the following conditions:

Occurrence of severe complications and/or general health deterioration (i.e., sepsis, bleeding, AV fistula occlusion, and progress of electrolyte disorders such as ECG change of hyperkalemia, or uncontrolled calcium × phosphorus (Ca × P) level);Occurrence of a severe adverse event (AE) of any type during the intervention;Voluntary withdrawal from the trial, absence from two consecutive interviews, or loss to follow-up.

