### Interventions

The CHM product investigated in this study will be prescription-grade JBT powder (Product code; NO.0321131, Ko Da Pharmaceutical Co., Ltd., Taoyuan, Taiwan) manufactured in accordance with Good Manufacturing Practices (GMP) and tested before factory release. Juan Bi Tang consists of 4 g *Rx. Angelica Sinensis*當歸, 4 g *Rx. Paeoniae Rubra*赤芍, 4 g *Rx. Astragali*黃耆, 4 g *Rz. Curcuma Longae*薑黃, 1 g *Rx. et Rz. Notopterygii*羌活, 4 g *Rx. Saposhnikoviae*防風, 3 g *Rz. Zingiberis Recens*生薑, 2 g *Fr. Zizyphi Jujube*大棗, and 1.5 g *Rx. Glycyrrhizae Preparata*炙甘草. These raw herb materials, together with starch excipient, are extracted and concentrated according to a standardized Chinese formula (see: http://www.koda.com.tw/tqm04_e.aspx). The participants will be instructed to take JBT orally in doses of 3 g (per bag) each time, thrice daily, for 4 weeks. Patients will return each week to the outpatient clinic for evaluation, medication, and counting of any unconsumed bags. Weekly compliance below 75% will be considered a deviation from the protocol and will lead to exclusion from further participation in the study. Participants in the non-treatment period will receive simple self-care measures for MPS based on the non-pharmacologic intervention in patients with CKD by Pham et al. (18). These will mainly include physical activities such as stretching, aerobic and strength exercises, and some types of combined exercises (18). The duration of the intervention will be 8 weeks, and the follow-up will be at 2 weeks.

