### Concomitant treatments

Routine medication for maintenance HD will be continued. The medication regimen will be recorded at every visit, and participants will need to inform the study assistant of any changes to their medication, supplements, and even exercise. Additional acupuncture, herbal prescriptions, or other interventions by other TCM practitioners will not be permitted during the treatment period.

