### Safety assessments

Juan Bi Tang is described in the ancient literature of TCM as relatively safe, and previous clinical studies have reported no major toxicity in therapeutic doses (37–39). However, we will still perform a series of measures to assess the safety of JBT throughout the entire trial due to possible herb-induced toxicity or herb-dialysis interaction (40). All safety-related variables, including vital signs, physical examination, hematological test, biochemical test, and AEs, will be recorded in the case report at every visit. Laboratory testing of the participants' blood, electrolytes (i.e., potassium, phosphorus, and calcium), albumin, parathyroid hormone, and kidney and liver function will be monitored before the intervention, at 2-week intervals during the intervention, and again at 2 weeks after trial completion. In addition, all details of AEs and other ailments will also be documented accurately at every study visit, including the occurrence time, severity, duration, effective measures, and transfer. Each AE associated with the intervention drugs will be classified as mild, moderate, or severe. If severe AEs such as hyperkalemia, thrombocytopenia, liver injury, bleeding, or cardiovascular events related to JBT occur during the study, the principal investigator will provide immediate diagnosis and treatment and report the AE to the Institutional Review Board within 24 h of the time of recognition. All AEs will be monitored and recorded by an independent researcher unassociated with the study until recovery of the participant.

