At present, the findings of most animal studies have confirmed the benefits of JBT in improving arthritis and synovitis (45–47). Significant reductions in the serum levels of MMP-2 and MMP-9 indicate that JBT has a role to play in preventing osteoarthritis (45). Similar effects of JBT on synovial inflammation and bone destruction through inhibiting the pro-inflammatory cytokines have recently been reported by Wang et al. (46). In addition, a study by Zhao et al. has demonstrated that JBT ameliorates bone destruction and reduces bone loss induced by rheumatoid arthritis (47). Therefore, it is possible that JBT may alleviate pain by not only improving blood flow but also down-regulating inflammatory markers. This study is designed to determine whether JBT is preferable to non-pharmacologic methods for the treatment of dialysis-related myofascial pain. If this trial produces the expected results, it will provide both patients and physicians an additional option for pain control. Moreover, this trial will provide preliminary data on the effects of JBT on arm power and motor function, QOL, and safety.

HD patients may receive 10–12 medications daily, and many of these medications require multiple doses each day. Drug–drug interactions are very common due to poly-pharmacy in HD patients (48), so the involvement of JBT therapy in drug interactions is an important issue for the therapeutic efficacy and safety of medical treatment. Although several studies have reported the possibility of herb–drug interactions in CKD patients leading to nephrotoxicity, electrolyte abnormalities, or changes in kidney hemodynamics (49, 50), very few studies have tested CHM with targeted safety assessments. It is worth noting that the *Rx. Angelica Sinensis* component of JBT may increase the risk of bleeding when heparin is used to prevent clotting in the dialytic extracorporeal circuit (51). In addition, excessive intake of *Rx. Glycyrrhizae Preparata* may lead to hypertension, hypokalemia, and metabolic alkalosis (52), which may cause myopathy and arrhythmia in HD patients. Thus, the results will contribute to herb repurposing for managing myofascial pain in patients receiving HD and will provide information useful for designing a large-scale randomized controlled trial in the future.

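### As printed, coagulopathy is excluded only when it is severe and disrupts attendance, although the article names bleeding with dialysis heparin as a possible hazard of JBT

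*Protocol article*

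**What the plan says.** The first item under Exclusion criteria in the protocol article is "Severe systemic disease (i.e., sepsis, cancer, coagulopathy) interfering with therapy attendance". No other inclusion or exclusion item names a clotting or bleeding disorder. Chronic liver disease is excluded in the next item with no attendance condition. Purpura is mentioned, but only as an allergic reaction to Chinese herbal medicine.

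On the hazard, the Discussion says that the Angelica "component of JBT may increase the risk of bleeding when heparin is used to prevent clotting in the dialytic extracorporeal circuit". Under Concomitant treatments, "Routine medication for maintenance HD will be continued". Safety assessments provides for serious events attributed to the product: "If severe AEs such as hyperkalemia, thrombocytopenia, liver injury, bleeding, or cardiovascular events related to JBT occur during the study", the principal investigator is to diagnose, treat and report them.

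On safeguards, Safety assessments says "All safety-related variables, including vital signs, physical examination, hematological test, biochemical test, and AEs, will be recorded in the case report at every visit", and has laboratory tests before the intervention and every 2 weeks during it. Table 1 shows laboratory data at week 0. Under Interventions, "Patients will return each week to the outpatient clinic for evaluation, medication, and counting of any unconsumed bags". Subject withdrawal criteria ends participation on "Occurrence of severe complications and/or general health deterioration (i.e., sepsis, bleeding, AV fistula occlusion" and similar events.

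**The concern.** An eligibility rule should screen on the property that makes a patient unsuitable. For sepsis or cancer, the printed item asks whether the illness would stop the patient coming to visits. For coagulopathy in a trial of a product with a stated bleeding concern, attendance is beside the point: a patient can come to every session and still be at raised risk of bleeding. Screening staff who apply the rule as written would have no ground to refuse such a patient.

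What is at stake is the safety of individual participants. Because the design is a crossover, drawing one group rather than the other does not spare a patient the product; it only changes when the course is due. No estimand, test or sample-size input depends on this point.

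**Working it through.** The article gives no figure to reproduce. The check is a reading of the rule against the sections that bear on it.

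**1. What the item requires.** The three diseases stand in parentheses between the noun phrase and its modifier, so both the severity term before them and the attendance condition after them apply to each. For coagulopathy this gives:

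| Coagulopathy severe? | Disrupts attendance? | Excluded by this item? |
|---|---|---|
| Yes | Yes | Yes |
| Yes | No | No |
| No | Yes | No |
| No | No | No |

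Only one of the four combinations is excluded. The second row is the main concern: a severe clotting disorder in a patient who attends.

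**2. Whether another criterion closes it.** The chronic liver disease exclusion catches coagulopathy of hepatic origin. Nothing else in the two lists catches other causes. Low platelets and anticoagulant or antiplatelet use are not listed either.

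**3. Whether the hazard belongs to the plan.** It does. The Discussion states it for one JBT ingredient together with circuit heparin, every participant is on thrice-weekly hemodialysis (Inclusion criteria), and routine dialysis medication continues. The article does not say how many participants receive heparin. That coagulopathy adds to this risk is a clinical inference; the article does not state it.

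**4. Whether exposure is certain once enrolled.** Study design gives group A the JBT course in period I and group B in period II. Both of the two sequences contain it, so an enrolled patient who stays in the trial is due to receive it.

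**5. What stands between entry and exposure.**
- Baseline laboratory tests come before any JBT. The named tests are blood, electrolytes, albumin, parathyroid hormone, and kidney and liver function. No coagulation test is named, and no result is linked to eligibility.
- Group B also has laboratory data at weeks 4 and 6, before its JBT course starts. A group B patient who bled severely in period I would be withdrawn before taking JBT.
- For group A, and for a group B patient who does not bleed in period I, the weekly evaluation and the bleeding withdrawal rule operate once treatment is under way.

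**6. Exposure arithmetic, and why it is not a measure of size.** Dosing is "in doses of 3 g (per bag) each time, thrice daily, for 4 weeks", which is 3 × 28 = 84 bags, or 84 × 3 g = 252 g per course, across 3 × 4 = 12 dialysis sessions. If heparin is assumed at every session there are 12 combined exposures; for heparin-free dialysis there are 0. These figures are the same for every participant. They describe the planned course and say nothing about excess bleeding risk in a patient with coagulopathy.

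**The case against.** The strongest reply is that this is loose drafting. Coagulopathy is named in the exclusion list beside sepsis and cancer, and on the literal reading a patient with sepsis who attends would also be eligible, which nobody can have intended. That stands as evidence of intent: the authors probably meant all three to exclude. It does not rescue the printed rule. The neighbouring items, such as chronic liver disease, stroke and psychiatric disorder, carry no attendance condition, so unqualified wording was available and was used elsewhere.

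A second reply is that the article condenses a fuller protocol in which eligibility terms may be defined. That lowers the chance that such a patient would actually be enrolled. But the point is not about absent detail: the criterion is printed and carries the wrong condition.

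A third reply is that the hazard is tentative, concerns one ingredient combined with heparin, and so applies to every heparinised participant; Safety assessments also cites earlier clinical studies without major toxicity at therapeutic doses. All of this stands. It limits how much weight the point can bear.

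A reader might infer that every safeguard comes after exposure, so that the entry rule is the only barrier. The article does not support that: laboratory tests precede the intervention, and the withdrawal rule can act before JBT in group B. The supportable statement is that none of these measures is set up to screen for coagulopathy.

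**Conclusion.** The point holds as a defect of wording with a safety consequence. Read literally, the criterion admits a patient with non-hepatic coagulopathy who attends reliably, and that patient is then scheduled for a product about which the article itself raises a bleeding concern.

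The size is small and cannot be quantified. The article gives no count of such patients, and it may be zero. The conclusion rests on the literal reading of the item and on two assumptions: that at least some participants receive circuit heparin, and that coagulopathy adds to any bleeding risk.

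Two stronger readings are not supported. The text does not show a decision to admit patients with coagulopathy. Nor does it show that JBT causes bleeding in them; the stated hazard is a possibility for one ingredient. The trial's statistical conclusions are not affected.

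**What to change.** Split the first exclusion item. Keep severe systemic disease that disrupts attendance, with sepsis and cancer as its examples, and add a separate item with no qualifier: *coagulopathy or active bleeding*. Apply it from the medical history at the existing screening visit.

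This is an edit to one line. It adds no visit, blood draw or procedure and leaves the sample size and analysis as they are. The downside is possibly a few more screen failures. It leaves the attendance condition on sepsis and cancer, and it does not change herb–heparin exposure for the remaining participants, for whom the existing monitoring and withdrawal rules continue to serve.
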